## Abstract

**Background::**

Cancer-related fatigue (CRF) is the most common and distressing symptom associated with cancer treatment that breast cancer survivors (BCS) experience. We previously found that laser moxibustion may be efficacious for CRF. The primary aim of this study is to determine the specific efficacy of 10.6 μm infrared laser moxibustion on CRF. The secondary aim is to evaluate the effect of infrared laser moxibustion on co-existing symptoms that BCS experience.

**Methods::**

We will conduct a randomized, sham-controlled, three-arm trial of infrared laser moxibustion (ILM) against sham ILM (SILM) and waitlist control (WLC) among BCS with moderate to severe fatigue. The two intervention groups will receive either real or sham infrared laser moxibustion on four acupoints (i.e., ST36 [bilateral], CV4, and CV6) for 20 minutes each session for 6 weeks (twice per week). The primary endpoint is the change in fatigue score from Baseline to Week 6 as measured by the Chinese version of the Brief Fatigue Inventory (BFI-C). Our secondary aim is to compare the severity of co-morbidities (e.g., depression, insomnia, and pain) among the 3 groups.

**Discussion::**

The results of our trial will establish evidence for the efficacy of infrared laser moxibustion for CRF, a very common and challenging symptom.

**Trial registration number::**

NCT03553355.

## Introduction

1

Cancer-related fatigue (CRF) is the most common and distressing symptom associated with cancer treatment. The prevalence of CRF ranges from 25% to 99% during active cancer treatment^[1,2]^ and it can persist for five to ten years after completion of treatment in approximately 30% of cancer survivors.^[3]^ Breast cancer is the most common cancer in women worldwide. Because of early detection and effective treatment, breast cancer survivors (BCS) constitute the largest population of cancer survivors.^[4,5]^ CRF contributes to impaired functioning and a decline in overall quality of life,^[6,7]^ and is a significant predictor of recurrence-free survival in BCS.^[8]^ Hence, the management of CRF to improve the quality of life in BCS is critically important.

Despite high levels of clinical significance, managing CRF is challenging.^[9]^ The effectiveness of pharmacologic treatments for CRF, including erythropoietin (e.g., epoetin, darbepoetin), psychostimulants (e.g., methylphenidate, modafinil), and anti-inflammatories (e.g., corticosteroids) is tenuous, and negative side effects are common and can be debilitating.^[10,11]^ Recently, integrative medicine therapies have emerged as promising non-pharmacological treatment options many cancer survivors use to reduce CRF.^[12,13]^ Further, a current systematic review suggests exercise or psychological interventions as first-line treatments for CRF.^[14]^ However, fatigue is a major barrier to starting or maintaining physical activity among cancer patients.^[15,16]^

Growing evidence suggests that acupuncture, a common integrative medicine treatment, may be safe and effective for managing CRF^[17–19]^ When it is delivered by adequately trained practitioners, acupuncture is generally considered to be a safe form of treatment.^[20,21]^ Moxibustion, a modality of acupuncture, is a noninvasive procedure that involves burning moxa, the herb *Artemisia vulgaris*, on or above the skin at acupoints. Instead of using the needle stimuli of acupuncture, moxibustion provides heat stimuli to alleviate symptoms; this method may be particularly appealing to patients who do not like the needle penetration associated with acupuncture.^[22]^ To our knowledge, research concerning the effects of moxibustion on CRF has only been reported in a few Chinese language articles and most of the studies had a high risk of bias, such as small sample size or no sham control.^[23]^ Furthermore, traditional moxibustion has several shortcomings, including air pollution and potential burning of the skin.

Infrared laser moxibustion, a novel noninvasive and painless therapy, mimics the effect of traditional moxibustion to irradiate on acupoints with a 10.6 μm infrared laser. It avoids the shortcomings of traditional moxibustion, such as smoke, unpleasant smell, and difficulty in controlling the dosage. Our previous study demonstrated that the specific wavelengths of infrared radiation produced by moxibustion were as potent as those generated by thermal radiation and that the peak wavelength of infrared radiation from conventional partitioned moxibustion was approximately 10 μm.^[24]^ In our preliminary study (N = 61), infrared laser moxibustion appeared to be safe and efficacious for improving CRF in a Chinese patient population.^[25]^ Building on this promising pilot data, we designed the current trial to evaluate the specific efficacy of infrared laser moxibustion on CRF in BCS.

## Specific aims and hypotheses

2

Our primary specific aim is to evaluate the efficacy of infrared laser moxibustion on CRF in BCS. We hypothesize that the Infrared Laser Moxibustion (ILM) group will have significantly greater improvement in the fatigue score from Baseline to Week 6 (primary end point) to Week 18 (follow up) compared to sham ILM (SILM) and waitlist control (WLC) groups. The primary outcome measure is the change over time in the mean score of the Chinese version of the Brief Fatigue Inventory (BFI-C).

Our secondary aim is to evaluate the efficacy of infrared laser moxibustion in insomnia, anxiety, depression, and pain among BCS experiencing CRF. We hypothesize that BCS with CRF randomized to ILM will have significantly greater improvement in insomnia, anxiety, depression, pain, and quality of life from Baseline to Week 6 and from Baseline to Week 18 compared to those randomized to SILM and WLC. Secondary outcome measures include the change over time in the mean score of the Chinese versions of the Pittsburgh Sleep Quality Index (PSQI), Hospital Anxiety and Depression Scale (HADS), Brief Pain Inventory (BPI), and Functional Assessment of Cancer Therapy-Breast (FACT-B).

Our exploratory mechanistic aim is to explore the effects of infrared laser moxibustion on telomere length among BCS with CRF. We hypothesize that BCS with CRF who are randomized to ILM will have a significantly greater increase in telomere length over time from Baseline compared to SILM and WLC.

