#### Primary Outcome

3.7.1

Our primary outcome is the fatigue score measured by the Chinese version of the Brief Fatigue Inventory (BFI-C).^[30,31]^ The scale score has excellent internal consistency of 0.96. The indicators of the scale assessment include the current level of fatigue; the fatigue level within the past 24 hours; and the impact of CRF on physical activities, emotions, ability to walk, ability to work, relationships with others, and enjoyment of life within the past 24 hours. The BFI-C uses 10-point numeric descriptions: scores of 1 to 3 represent mild levels of fatigue, scores of 4 to 6 represent moderate levels of fatigue, and scores of 7 to 10 represent severe levels of fatigue. The endpoint is the change in fatigue score from Baseline to Week 6 (end of treatment) among the 3 groups.

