We have based our sample size calculation on our preliminary study. We plan to enroll and randomize 140 participants (2:2:1) to ILM, SILM, and WLC. Assuming a 20% attrition rate, we will have 45 participants in each of the ILM and SILM groups and 22 participants in the WLC group who will provide evaluable outcomes. In our previous study, we found that ILM produced a greater reduction in BFI-C intensity at the end of intervention (Week 4 from baseline) at a magnitude of 0.60 SD (Standard Deviation) as compared to SILM. Given an alpha of 5%, with 45 subjects in each of the ILM and SILM groups, we will be able to detect a between-group difference of reduction in BFI-C of 0.60 SD with 80% power. With 45 subjects each in the ILM and SILM groups and 22 participants in the WLC group, a power of 80% and two-sided alpha of 0.05, we will be able to detect an effect size of 0.71 SD (i.e., difference of reduction in BFI-C) between ILM and WLC or SILM and WLC groups. This is a conservative way to estimate sample size since the longitudinal analysis using all repeated measures with the mixed-effects model specified in the analysis plan will provide higher power than a *t* test.

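### The primary hypothesis names two comparators, sham and waitlist, each planned at a full 5% with 80% power, and the protocol does not say which contrast decides the trial

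*Protocol article*

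**What the plan says.** Section 2 (Specific aims and hypotheses) predicts significantly greater improvement in fatigue with ILM "compared to sham ILM (SILM) and waitlist control (WLC) groups". Both comparators sit in one primary hypothesis.

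Section 3.7.1 (Primary Outcome) names no contrast: "The endpoint is the change in fatigue score from Baseline to Week 6 (end of treatment) among the 3 groups".

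Section 3.15 (Statistical analysis and sample size calculation) tests differences between arms through time-by-intervention interactions in mixed models. It gives no test level there, no order and no split of alpha. Its sample-size paragraph treats the contrasts one at a time:
- ILM vs SILM: "Given an alpha of 5%, with 45 subjects in each of the ILM and SILM groups", the trial can "detect a between-group difference of reduction in BFI-C of 0.60 SD with 80% power".
- ILM vs WLC, and equally SILM vs WLC: "a power of 80% and two-sided alpha of 0.05, we will be able to detect an effect size of 0.71 SD".

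Other sections point towards the sham contrast. The Abstract and the end of the Introduction give the aim as specific efficacy. The Discussion says the arm without sham was added to gauge the overall effect.

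**The concern.** A primary hypothesis with two contrasts needs a rule for success: one named contrast, either of them, or both. The protocol gives none, and the choice changes what its planning figures mean. If either contrast can carry the hypothesis, two tests at 5% do not hold the overall error at 5%. If both must succeed, 80% per contrast is not 80% for the hypothesis.

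The two contrasts are also not equivalent evidence. Section 3.6 (Masking) masks participants between real and sham treatment but not between treatment and waitlist, and the outcome is self-reported fatigue. A difference from waitlist can therefore reflect expectation as well as the laser. The text as written would let a result against waitlist alone be presented as meeting part of a primary hypothesis whose aim is specific efficacy.

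**Working it through.** **Inputs (Section 3.15).** "We plan to enroll and randomize 140 participants (2:2:1) to ILM, SILM, and WLC" gives 56/56/28. With 20% attrition this is 56 × 0.8 = 44.8 and 28 × 0.8 = 22.4, which agrees with the stated 45/45/22. Effects are 0.60 SD (ILM–SILM) and 0.71 SD (ILM–WLC), and alpha is 0.05 per contrast.

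**Step 1. Reproduce the plan's figures.** Power ≈ Φ(δ/SE − 1.960), with SE = √(1/n₁ + 1/n₂) in SD units.
- ILM vs SILM: SE = √(2/45) = 0.211; 0.60/0.211 = 2.846; power = Φ(0.886) = 81.2% (80.4% with the t distribution). The stated 80% reproduces as a two-sided figure; one-sided it would be 88.5%.
- ILM vs WLC: SE = √(1/45 + 1/22) = 0.260; 0.71/0.260 = 2.729; power = Φ(0.769) = 77.9% (76.7% with t). This is slightly under the stated 80%, which needs 0.73 SD (normal) or 0.74 SD (t). That is a small separate point.

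**Step 2. Correlation of the two tests, which share the ILM arm.** ρ = (1/45) / √[(2/45)(1/45 + 1/22)] = 0.405.

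**Step 3. If either win is enough.** Simulation of the three arm means under the global null (2 million draws, 45/45/22):
- P(|Z₁| > 1.960 or |Z₂| > 1.960) = 9.3%. For independent tests it would be 1 − 0.95² = 9.75%.
- Counting only false claims that ILM is better: 4.7%, against a nominal 2.5%.

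**Step 4. If both wins are needed.** There is no inflation of alpha. Joint power is P(Z₁ > 1.960 and Z₂ > 1.960), from the same simulation and checked at 0.71 and 1.00 SD with the bivariate normal distribution. The true ILM–SILM effect is held at 0.60 SD. The document gives no expected ILM–WLC effect, so it is varied:

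| True ILM–WLC difference (assumed) | Power to win both |
|---|---|
| 0.60 SD | 56% |
| 0.71 SD | 67% |
| 0.80 SD | 73% |
| 0.90 SD | 78% |
| 1.00 SD | 80% |
| 1.20 SD | 81% |

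**Step 5. What each remedy costs.**
- Fixed sequence, ILM vs SILM then ILM vs WLC, each at 0.05: family-wise error 5%, sham-contrast power still about 81%, N = 140.
- Bonferroni at 0.025 each: power 72.7% against SILM and 68.7% against WLC; about 53 evaluable per ILM and SILM arm would be needed for 80% against SILM.
- Both must win, with 80% joint power at 0.60/0.71 SD: about 143 evaluable, or 143/0.8 ≈ 180 randomized.

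**The case against.** The strongest reply is that success rules and alpha allocation usually sit in an analysis plan, which is not shown, and that this is a condensed article. The 5% levels are sample-size inputs and not a stated decision rule. That much stands: a reader might infer that the trial will run at a 9% error rate, but the article never says that either win suffices, and the word 'and' in Section 2 points the other way. What remains is not mere silence. The protocol itself puts both contrasts in the primary hypothesis, and which of them decides the trial is part of defining that hypothesis.

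A global three-group test followed by pairwise tests would also fit Sections 3.7.1 and 3.15, and with three groups it would hold the family-wise error at 5%. The article does not state this procedure, and it would still not say which contrast decides.

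The aim and the described role of the waitlist arm do signal that the sham contrast leads. They fall short of making it first or sole, but they show that the fix fits the investigators' intent.

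Three further readings are tempting and unsupported:
- A 12.1% error rate. This adds SILM vs WLC, which is outside the primary hypothesis.
- A 78% chance of a false primary success. With no effect over sham and 0.71 SD over waitlist, ILM beats at least one comparator in about 78% of trials. ILM truly differs from waitlist in that scenario, so this is not an error rate.
- A wrong 80%. Section 3.15 states power per contrast and never claims it for the two together.

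Joint power well below 80% is also not certain. If expectation makes the waitlist difference large, most of the shortfall disappears.

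**Conclusion.** The point holds as a defect in how the primary hypothesis is fixed, not as proof of an inflated error rate. On the conjunctive reading, which the wording favours, the trial has about 67% power for its primary hypothesis at 0.60 and 0.71 SD. The range is 56% to about 80% as the true waitlist difference goes from 0.60 to 1.00 SD. On the either-suffices reading, two-sided family-wise error is about 9.3%, or 4.7% against 2.5% in the favourable direction. These figures assume 45/45/22 evaluable participants, a common SD, a comparison of changes at one time point, and the global null for the error rates. A mixed model using all visits may give somewhat more power, as Section 3.15 itself expects, but it does not settle which contrast decides. The matter should be resolved, and it needs no change to the design.

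**What to change.** In Sections 2, 3.7.1 and 3.15, state that:
1. ILM vs SILM in change in BFI-C from Baseline to Week 6 is the sole primary comparison, at two-sided 0.05.
2. ILM vs WLC at Week 6 is tested at two-sided 0.05 only if the first comparison is significant; otherwise it is reported as an estimate with its confidence interval.
3. SILM vs WLC is reported as an estimate with its confidence interval, outside the confirmatory family.

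This takes a sentence or two and should be recorded before any unblinded comparison. It holds the family-wise error of the two ILM contrasts at 5%. The one real cost is that if ILM vs SILM fails, no confirmatory claim against waitlist can be made, however large that difference is.

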## Methods

3

### Study design

3.1

We will conduct a randomized controlled, 3-arm trial of ILM compared to SILM and WLC for moderate (score of 4–6 on BFI-C) to severe (score of 7–10) fatigue in BCS. After random assignment to 3 groups, patients in the ILM and SILM groups will receive 20-minute treatments of real/sham infrared laser moxibustion twice per week for six weeks. We will have a 12-week follow-up period to evaluate the durability of the treatment effects. We will assess patient-reported fatigue and other comorbid symptoms at Baseline, Weeks, 6, 12, and 18, respectively. We have included details of the study timeline in Figure 1. This study was approved by the Institutional Review Board of Yueyang Hospital and registered with the identifier NCT03553355 (12 June 2018) at ClinicalTrials.gov. All participants will provide written informed consent.

**Figure 1 F1:**
[figure not shown]
Study timeline.

Recruitment started in June 2018 and will continue until December 2019. We will follow the Consolidated Standards of Reporting Trials (CONSORT) guidelines for reporting on nonpharmacological treatment interventions^[26]^ and the Standards for Reporting Interventions in Clinical Trials of Acupuncture (STRICTA).^[27]^

### Participants

3.2

Eligible study participants will be female breast cancer survivors (stage I–III), aged 18 years and older, who are at least 12 weeks post primary treatment (e.g., surgery, chemotherapy, and radiotherapy) and have complained of persistent, moderate to severe fatigue despite having the ability to rest. We will interview participants to ensure that they meet the International Classification of Diseases-10 diagnostic criteria for CRF.^[28]^ We will screen participants using the National Comprehensive Cancer Network (NCCN) clinical guidelines for CRF^[29]^ and an item asking respondents to rate their level of fatigue over the past seven days on a scale of 0 (“no fatigue”) to 10 (“worst fatigue you can imagine”) with a score of 4 as the cutoff point. We will exclude treatable etiologies (e.g., anemia and hypothyroidism). We have detailed our eligibility criteria along with the source of that material and the study personnel responsible for determining that criteria in Table 1

**Table 1 T1:**
[figure not shown]
Eligibility criteria and source document.

### Recruitment and enrollment

3.3

We will recruit patients from oncology clinics at Yueyang Hospital affiliated with the Shanghai University of Traditional Chinese Medicine in Shanghai, China. We will post clinical trial information on notice boards in this hospital and release recruitment notices on flyers and social networks. We will also contact the oncology physicians for referral of their potentially eligible patients. Then we will contact the potential participants via telephone triage and interview them to determine final and overall eligibility. We will conduct and obtain informed consent at the first interview. Following consent, we will collect baseline patient-reported outcomes and clinical data.

### Randomization and allocation concealment

3.4

We will randomize participants to ILM, SILM, or WLC groups with an allocation ratio of 2:2:1. The biostatistician will conduct allocation using permuted block randomization with varying block sizes, stratified by age (<50/≥50 years of age) and baseline fatigue level (<7/≥7). The randomization sequence generation will be completed prior to the recruitment of participants and the investigators will remain blinded to the treatment condition. Randomization information will be sealed in opaque envelopes that we will open after participants complete their baseline assessment.

### Interventions

3.5

#### Infrared laser moxibustion therapy

3.5.1

We will use SX10-C1 laser moxibustion devices (Shanghai Wonderful Opto-Electrics Tech Co. Ltd., Shanghai, China) for the ILM and SILM groups. Four laser probes will be simultaneously aligned with four points (ST36 [bilateral], CV4, and CV6 acupoints) and we will irradiate each acupoint 2 cm away from the skin surface for a total of 20 minutes. Each patient will receive this treatment twice per week for six weeks (12 session total).

#### Sham infrared laser moxibustion therapy

3.5.2

Patients in the SILM group will adhere to the same treatment protocol as those in the ILM group. The sham laser moxibustion instrument appears to be identical to the real one. However, in the sham group, no laser will be released when the instrument is turned on. Because the infrared laser is colorless, neither the operator nor the patients can see it, so the procedure will be double-blinded.

#### Waitlist control

3.5.3

The participants in the WLC group will not receive real or sham laser moxibustion treatment. They will maintain their usual treatment and self-care, but will not begin any additional treatment to improve their cancer-related fatigue during the study. In addition, we will inform them that they will receive ten real laser moxibustion treatments after completing the study follow-up period.

We will not restrict medications study participants may use. We will enter patients’ previous medications in the database. In the event that during the study a patient starts a new regimen that might affect their fatigue severity, we will do sensitivity analyses to exclude this participant.

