### Outcome measures

3.7

Outcome measures and data collection time points are listed in Table 2. The primary endpoint of this study is the post-intervention assessment (T2, after 6 weeks of treatment sessions). We will measure primary and secondary outcomes at baseline (T0), mid-intervention (T1, after 3 weeks of treatment sessions), post-intervention (T2) and at follow-up (T3 and T4, 6, and 12 weeks after 6 weeks of treatment sessions). The collected clinical data will be collected with REDCap.

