### Statistical analysis and sample size calculation

3.15

Standard descriptive statistics will be used to analyze baseline participant characteristics. We will produce summary statistics such as means, medians, standard deviations, and ranges for measured variables. We will tabulate frequencies for categorical and ordinal variables. We will use graphical methods extensively to examine distributions, identify potentially influential points, and guide data transformations if warranted. For continuous variables with markedly non-normal or skewed distributions, appropriate transformation may be required, such as natural logarithms, which we will apply as necessary and appropriate.^[43]^ In the sections below, we will assume, when discussing particular outcomes, that the appropriately transformed variables will be used. We will perform analysis according to the intention-to-treat (ITT) principle (i.e., subjects will be analyzed according to the treatment group to which they will be randomly allocated regardless of drop-out).

To determine the effects of ILM on fatigue, we will use mixed effects models.^[44]^ This statistical procedure takes into account within-subject correlations from repeated measurements in the same subjects and allows estimation of between-group difference without necessitating that the last observation is carried forward or exclusion of participants with missing data. Tests of ITT differences between intervention arms with respect to change in BFI-C will be based on time-intervention interactions in the mixed-effects models. Although randomization theoretically balances the potential confounders between treatment groups, occasional unequal distribution can be seen. Should this happen, the effect of confounding will be evaluated by including the potential confounders as co-variates in the models.^[43]^ For secondary outcomes, we will use similar analytical strategies for co-morbid symptoms. To evaluate the long-term durability of treatment effect, we will display long-term data descriptively. It is possible that the long-term outcome may display different patterns from short-term therapeutic effect. If this occurs, we may need to create piece-wise linear mixed-effects models to fit the data and test for statistical significance on outcome change among treatment groups.

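### The new-regimen sensitivity analysis drops whole participants for starts at any time, so it discards Week 6 values that a later start could not have affected (minor)

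*Protocol article*

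**What the plan says.** The rule stands in the protocol article, section 3.5.3 (Waitlist control), after a statement that medication use is not restricted.

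- **Trigger:** the rule applies if "during the study a patient starts a new regimen that might affect their fatigue severity". No time window is given.
- **Unit removed:** "we will do sensitivity analyses to exclude this participant". The person is removed, not the values recorded after the start.

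The timing comes from other sections.

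- **Primary endpoint:** section 3.7.1 (Primary Outcome) says "The endpoint is the change in fatigue score from Baseline to Week 6 (end of treatment) among the 3 groups".
- **Later visits:** section 3.7 (Outcome measures) places further assessments "at follow-up (T3 and T4, 6, and 12 weeks after 6 weeks of treatment sessions", that is, at Weeks 12 and 18. Section 3.1 (Study design) says "We will have a 12-week follow-up period to evaluate the durability of the treatment effects".
- **Primary analysis:** section 3.15 keeps everyone in the arm assigned: "subjects will be analyzed according to the treatment group to which they will be randomly allocated regardless of drop-out". It uses mixed effects models, chosen partly because they do not require dropping participants with missing data.

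No other section narrows the trigger or the unit of the exclusion.

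**The concern.** The purpose of this analysis is to show whether new co-treatment explains the fatigue result. For the Week 6 comparison, only regimens started before the Week 6 visit can have changed the recorded score. The rule also catches starts in the following 12 weeks and removes those participants' Week 6 scores.

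This has two consequences. First, valid data are lost and the analysis becomes less precise. Second, starting a new regimen happens after randomisation and may follow from poor response. Patients enter with moderate to severe fatigue and medication is unrestricted, so those still fatigued have a reason to try something else. Excluding them trims poor responders, and more of them in the less effective arm.

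If this analysis then disagrees with the intention-to-treat result, a reader cannot tell how much reflects co-treatment and how much reflects selection or lost data.

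**Working it through.** **Inputs from the protocol article (3.15).** 140 randomised 2:2:1, 20% attrition, 45 evaluable in each of ILM and SILM, a difference of 0.60 SD, alpha 5%, power 80%.

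**The plan's own figure.** 56 × 0.8 = 44.8 per active arm, which rounds to the stated 45. With 45 per arm and 0.60 SD, two-sided power is 0.812 by the normal approximation and 0.804 by the t test. The stated 80% reproduces.

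**Exposure.** The study lasts 6 + 12 = 18 weeks. Starts in 12 of those 18 weeks, two thirds of the time, come after the Week 6 value is recorded.

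**Assumptions (the article gives no start rates).** All starts fall after Week 6. The start rate in the comparator (SILM) is p = 5%, 10% or 15%. The tendency to start has correlation k with a poor Week 6 change. One start threshold applies in both arms. The true difference is 0.60 SD.

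**Step 1: shift in the estimate.** Write φ for the standard normal density. With cut z in the comparator, the cut relative to the ILM mean is z + 0.60k, and p₁ is the resulting ILM start rate. Excluding starters improves each arm's mean by k·φ(cut)/(1 − start rate). The remaining difference is

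0.60 − k·φ(z)/(1 − p) + k·φ(z + 0.60k)/(1 − p₁).

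For p = 15% and k = 0.5, z = 1.036. The ILM cut is 1.336 and p₁ = 9.1%. The two terms are 0.137 and 0.090, so the estimate is 0.60 − 0.137 + 0.090 = 0.553 SD. Week 6 values removed: 45 × (0.15 + 0.091) = 10.8 of 90.

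Simulation with 4 million draws per arm agrees with the formula to about 0.002:

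| Comparator starts | Estimate after exclusion, k = 0.3 / 0.5 / 0.7 (SD) | Week 6 values removed of 90 |
|---|---|---|
| 5% | 0.590 / 0.576 / 0.557 | 3.8 / 3.4 / 3.1 |
| 10% | 0.585 / 0.565 / 0.532 | 7.7 / 7.1 / 6.5 |
| 15% | 0.582 / 0.552 / 0.512 | 11.8 / 10.8 / 10.0 |

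The shift runs from 0.60 − 0.590 = 0.01 to 0.60 − 0.512 = 0.09 SD. The standard error is √(2/45) = 0.21 SD.

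**Step 2: lost significance.** In 200,000 simulated trials of 45 against 45, these are the percentages of intention-to-treat-significant trials in which the exclusion test is not significant:

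| Comparator starts | k = 0 (data loss only) | k = 0.3 / 0.5 / 0.7 |
|---|---|---|
| 5% | 4.6% | 4.9 / 6.1 / 7.9% |
| 10% | 7.9% | 8.4 / 10.2 / 12.9% |
| 15% | 11.4% | 11.7 / 14.1 / 17.6% |

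Data loss alone accounts for about 5 to 11%. Selection adds between 11.7 − 11.4 = 0.3 and 17.6 − 11.4 = 6.2 points. The split is approximate, because at k = 0 both arms lose the full rate (for example 2 × 45 × 0.15 = 13.5 values).

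**Step 3: no true difference.** Equal, similarly selected starts give no bias. With 5% against 15% starts the shift is k·[φ(1.036)/0.85 − φ(1.645)/0.95], which is 0.041, 0.083 or 0.124 SD at k = 0.25, 0.5 or 0.75.

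**Step 4: the remedy.** A mixed model with a random intercept and visit as a category was fitted with 3,000 per arm, 15% late starts and k = 0.5. The Week 6 difference was 0.610 on all data, 0.550 after exclusion, and 0.610 with only post-start values set to missing. For starts between Weeks 3 and 6 (assumed Week 3 difference 0.30 SD, Week 3 to Week 6 correlation 0.5), exclusion gave 0.565 to 0.596 and set-to-missing 0.574 to 0.601, so the gain there is small.

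**The case against.** The strongest reply is that this is one sentence in a condensed article. A full analysis plan could set start windows for each visit, and the sentence never says outright that a Week 14 starter leaves the Week 6 comparison. That reduces the weight of the point but does not remove it. The article does not leave the matter open: it fixes a trigger without a window and a unit of exclusion, and a plan that followed it would carry both forward.

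Three further objections stand.

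- **Late starts are not irrelevant to the trial.** Section 2 (Specific aims and hypotheses) extends the hypotheses to Week 18. For Weeks 12 and 18 a late start can affect the scores, and handling it there is reasonable.
- **A reader might infer that no part of a changed Week 6 estimate could reflect co-treatment when all starts come after Week 6.** That holds for the recorded score. It need not hold for a model estimate: section 3.15 tests time-by-intervention interactions, contemplates piece-wise linear models and does not say that visit is categorical. With continuous time, affected Week 12 and 18 scores can enter the fitted Week 6 contrast.
- **The size is modest and assumed.** Most of the lost significance is plain data loss, the shift is below half a standard error, and nothing in the article makes significance of this analysis a decision rule.

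**Conclusion.** The point holds as a minor one. Followed as written, the rule discards Week 6 scores that a later regimen could not have affected, and it selects on an event that may depend on response. The harm is mainly avoidable loss of data in one supplementary analysis, with a small selection effect on top.

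The figures rest on assumed late-start rates of 5 to 15%, assumed correlations of 0.3 to 0.7, all starts after Week 6, one start rule in both arms and a true difference of 0.60 SD.

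A reader might also infer that the primary result is biased or that the trial's conclusion is at risk. The article does not support that: the primary analysis follows the intention-to-treat principle and the exclusion is confined to sensitivity analyses.

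**What to change.** In section 3.5.3, replace the exclusion of the participant with: *keep every randomised participant, set to missing only BFI-C values recorded after the start of the new regimen, and refit the same mixed model with visit as a category*. Use one definition of a relevant regimen in all three arms, judged blind to arm and outcome.

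If exclusion is kept, the minimum change is to count only regimens started before the Week 6 visit in the Week 6 comparison. Later starts should still be counted for the Week 12 and Week 18 comparisons.

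The cost is a sentence or two of wording and a recorded start date for each new regimen, which the present rule already requires staff to identify. Values after the start are assumed missing at random, so for starts before Week 6 bias may remain and the gain over exclusion is small.
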